# Chinese herbal medicine Tangshen Formula treatment of patients with type 2 diabetic kidney disease with macroalbuminuria: study protocol for a randomized controlled trial

**DOI:** 10.1186/s13063-016-1385-2

**Published:** 2016-05-23

**Keywords:** Chinese herbal medicine, Diabetic kidney disease, Macroalbuminuria, Randomized controlled trial, Tangshen Formula

## Abstract

**Background:**

Diabetic kidney disease (DKD) is one of the most common microvascular complications of diabetes mellitus and the main cause of end-stage renal disease. Present medications for DKD are not entirely satisfactory. Preliminary studies indicate that the Chinese herbal formula Tangshen Formula (TSF) appears to decrease the proteinuria and improve the estimated glomerular filtration rate (eGFR) in DKD patients.

**Methods/design:**

This trial is a five-center, randomized, double-blind, placebo-controlled study. DKD patients with a 24-h urinary protein (24 h UP) level between 0.5 and 3.5 g and serum creatinine < 265 μmol/L (3 mg/dl) will be included. A sample size of 144 participants will be randomly distributed into the treatment group (TSF plus irbesartan) and the control group (placebo plus irbesartan) at a ratio of 1:1. The study duration will be 50 weeks, comprising a 2-week run-in period, 24 weeks of intervention, and 24 weeks of follow-up. The primary endpoint will be the 24 h UP. Secondary endpoints will be an evaluation of renal function, management of blood lipids, improvement in traditional Chinese medicine symptoms, and safety assessments. Adverse events will also be evaluated.

**Discussion:**

This study will provide evidence for the effectiveness and safety of TSF compared to placebo in treating DKD patients with macroalbuminuria.

**Trial registration:**

Chinese Clinical Trials Registry, ChiCTR-TRC-13003566. Registered 9 August 2013.

**Electronic supplementary material:**

The online version of this article (doi:10.1186/s13063-016-1385-2) contains supplementary material, which is available to authorized users.

## Background

Diabetic kidney disease (DKD) is a major microvascular complication of both type 1 and type 2 diabetes mellitus (DM) [1]. However, in type 1 diabetics, DKD typically does not present until the second decade after diagnosis of diabetes, whereas in some type 2 diabetics, DKD is already evident at the time of diagnosis of diabetes because of other chronic instigators of kidney injury such as aging, hypertension, and abnormal lipid levels [2, 3]. In China, DKD is the second leading cause of end-stage renal disease (ESRD) after glomerulonephropathy [4] and is a leading cause of dialysis in developed countries such as Japan and the USA [5, 6]. The economic burden of DKD is substantial [7, 8]. Angiotensin-converting enzyme inhibitors (ACEIs) and angiotensin receptor blockers (ARBs) have been the agents of choice in slowing the progression of DKD. However, as seemingly effective as they are, these drugs have side effects such as rhinitis, persistent cough, and angioedema, which cause patients to discontinue therapy in some cases [9, 10]. Thus, it is clear that an unmet need exists for developing renoprotective therapies that are not only effective but also well tolerated.

Recent studies appear to show that certain Chinese herbs have renoprotective effects against chronic kidney disease (CKD) [11] and DM [12]. Hence, to assess the efficacy and safety of these herbs in DKD treatment, a well-designed, randomized, controlled trial (RCT) is needed.

Traditional Chinese medicine (TCM) is a medical system founded on syndrome pattern differentiation. Clarifying the main TCM syndrome type of DKD is essential for its treatment. We employed the Delphi method to investigate the most common signs and symptoms of DKD as propounded by TCM nephrology experts. From three rounds of questionnaires, we concluded that deficiency of both *qi* and *yin* with blood stasis is the main TCM syndrome type of DKD [13]. This result was in accordance with findings of other studies [14, 15] and was verified in our subsequent cross-sectional study of 350 DKD patients [16]. Based on this main syndrome type and empirical evidence from Chinese medicine practitioners, the herbs in Tangshen Formula (TSF) were chosen to treat DKD. The TCM function of the herbs in TSF is to replenish *qi* and *yin* and to promote blood circulation. Ensuing studies suggested that TSF treatment could decrease the urinary albumin excretion rate (UAER) and reduce glomerulosclerotic and interstitial fibrosis indices in both Otsuka Long-Evans Tokushima fatty (OLETF) spontaneously diabetic rats [17] and streptozotocin combined with uninephrectomy-induced type 1 diabetic rats [18]. Further research indicated that in DKD rats, the therapeutic effects of TSF might at least be partially due to its anti-inflammatory action of downregulating tumor necrosis factor α and upregulating pro-inflammatory cytokine interleukin-10 [19], as well as its antifibrotic action of inhibiting expression of transforming growth factor beta 1 (TGF-β1) in renal tissue, enhancing the expression of matrix metallopeptidase 9 (MMP-9), and reducing the expression of collagen type IV [18]. Another study of ours also found that TSF appears to exert a renal protective effect by improving lipid metabolism [20]. Our preliminary RCT indicated that TSF treatment might improve eGFR and decrease proteinuria, especially in patients with macroalbuminuria [21].

The current study is designed to validate whether or not TSF is safe and efficacious in the treatment of DKD patients with macroalbuminuria.

## Methods/design

### Ethics, consent, and permissions

The protocol (version identifier: TSF-3.0 (20130512)) has been approved by the ethics committee of the China-Japan Friendship Hospital (Approval No. 2013–46) and is registered with the Chinese Clinical Trial Registry (http://www.chictr.org.cn) under registration number ChiCTR-TRC-13003566. The study will be conducted in accordance with the principles of good clinical practice, i.e., the Declaration of Helsinki (2004 version). The trial will be reported according to the Standard Protocol Items: Recommendations for Intervention Trials (SPIRIT) (see Additional file 1). All patients will be informed about the purpose of the trial, the risks, and the benefits, and informed consent (see Additional file 2) will be obtained from all participants prior to entry into the trial. All visits will be documented in a case report form (CRF).

### Study design and setting

This trial will be a randomized, placebo-controlled, multicenter trial with two parallel groups. Investigators, the statistician, and participants will be blinded. The trial flow is illustrated in Fig. 1. Five hospitals in China will participate in the study: the China-Japan Friendship Hospital, Beijing; the First Teaching Hospital of Tianjin University of Traditional Chinese Medicine, Tianjin; the Hangzhou Hospital of Traditional Chinese Medicine Affiliated to Zhejiang University of Chinese Medicine, Hangzhou; the Shaanxi Provincial Hospital of Traditional Chinese Medicine, Xi’an; and the Longhua Hospital Affiliated to Shanghai University of Traditional Chinese Medicine, Shanghai.

**Fig. 1 Fig1:**
[figure not shown]
Flow diagram of progress through the study

### Eligibility criteria

#### Diagnostic criteria

The diagnosis of type 2 diabetes will be based on the American Diabetes Association (ADA) criteria [22], and DKD will be defined by the National Kidney Foundation Kidney Disease Outcomes Quality Initiative (NKF K-DOQI) guidelines [23].

#### TCM syndrome pattern differentiation

The Chinese syndrome pattern differentiation type of deficiency of both *qi* and *yin* with blood stasis will be based on guidelines delineated in *Clinical Research of New Investigational Drugs in Traditional Chinese Medicine* [24]. The diagnostic standards are as follows:Primary signs and symptoms include fatigue, listlessness, weakness, and soreness of the low back and knees; heat sensation in the palms and soles; and dry mouth and throat.Secondary signs and symptoms include catching cold easily, pale complexion, irritability, numbness, edema, frequent urination at night, constipation, and hematuria.

Participants will be diagnosed with deficiency of both *qi* and *yin* with blood stasis syndrome if they have two or more of the primary signs/symptoms and at least two of the secondary signs/symptoms. Investigators at each center will administer a symptom assessment survey to every participant (Table 1). This will ensure standardized scoring across centers.

**Table 1 Tab1:** Traditional Chinese medicine (TCM) symptom assessment survey

Fatigue	□ 0: None □ 2: Cannot sustain heavy work □ 4: Can manage mild intensity work □ 6: Can only do daily activities
Weakness and soreness of the low back and knees	□ 0: None □ 2: Occasional □ 4: Need to alter body position for relief □ 6: Persistent pain, need to take pain medication
Heat sensation in the palms and soles	□ 0: None □ 2: Occasional □ 4: Desire to expose extremities □ 6: Desire to hold something cold
Dry mouth and throat	□ 0: None □ 2: Mild □ 4: Decreased saliva production □ 6: Severe thirst with constant need to drink fluids
Qi deficiency and listlessness	□ 0: None □ 2: Shortness of breath after mild activity □ 4: Shortness of breath after moderate activity □ 6: Unable to talk or catch breath even without activity
Catch cold easily	□ 0: No colds □ 1: At least 6 times per year □ 2: At least 10 times per year □ 3: 12 or more times per year
Pale complexion	□ 0: None □ 1: Mild □ 2: Moderate □ 3: Pale or dark yellow complexion
Irritability	□ 0: None □ 1: Occasional □ 2: Easily irritated, but able to gain self-control □ 3: Severe agitation, unable to gain self-control
Numbness	□ 0: None □ 1: Hands and feet □ 2: Limbs □ 3: Entire body
Edema	□ 0: None □ 1: Palpebral edema in the morning □ 2: Palpebral and lower limb edema □ 3: Extreme generalized edema (hyposarca)
Frequency of urination at night	□ 0: None □ 1: 2 times □ 2: 3 to 4 times □ 3: 5 times or more
Constipation	□ 0: None □ 1: Hard stools and straining □ 2: Hard stools with a 2 to 3 days between bowel movements □ 3: Hard stools with 3 or more days between bowel movements
Hematuria	□ 0: None □ 1: Yes

After being screened for inclusion and exclusion criteria (Table 2), eligible patients will be entered into the trial.

**Table 2 Tab2:** Eligibility criteria

Inclusion criteria	Exclusion criteria
• DKD diagnostic criteria: a) Type 2 diabetes b) Diabetic retinopathy c) 24-h urinary protein (24 h UP) 0.5–3.5 g • Serum creatinine <265 μmol/L (3 mg/dl) • Controlled hypertension (blood pressure ≤ 130/80 mmHg) • A1C ≤ 8.0 • Chinese syndrome differentiation of *qi* and *yin* deficiency with blood stasis • Taking irbesartan (300 mg daily) continuously in the past 2 weeks • Between 18 and 70 years of age • Sign informed consent	• Blood pressure < 90/60 mmHg • Serum potassium > 5.5 mmol/L or < 3.5 mmol/L • Doubling of serum creatinine in the past 6 months • Renal artery stenosis • Severe diabetes complications or serious macrovascular events within 6 months (e.g., cerebral hemorrhage, massive cerebral infarction, or acute myocardial infarction) • Recent infection in the past 4 weeks • Other primary or secondary renal diseases (e.g., IgA nephropathy, membranous nephropathy, or lupus nephritis) • Any malignancy • Severe mental disorder • Pregnant or lactating women or women with the intention of becoming pregnant or women who are not using appropriate contraceptive methods • Allergic to components of agents used in the study • Participation in other clinical trials

### Interventions

Eligible participants will be randomized to either the TSF or placebo group, receiving oral administration of either TSF or placebo (12 g per packet) twice daily for 24 weeks.

TSF consists of seven natural herbs: astragalus root (*Astragalus membranaceus* (Fisch.) Bge.), rehmannia root (*Rehmannia glutinosa* (Gaertn.) Libosch.), notoginseng root (*Panax notoginseng* (Burk.) F. H. Chen), winged burning bush twig (*Euonymus alatus* (Thunb.) Sieb*.*), Asiatic cornelian cherry fruit (*Cornus officinalis* Sieb. Et Zucc.), rhubarb root and rhizome (*Rheum palmatum* L.), and bitter orange (*Citrus aurantium L.*).

Both TSF (Lot No. 1206388) and the placebo were manufactured by the Jiangyin Tianjiang Pharmaceutical Company (Jiangyin, China). The manufacturing process was quality controlled for physical characteristics, purity, microbial content, and weight consistency of the packets. Certificates of quality for the manufacturing of TSF and placebo have been provided by the manufacturer (Additional file 3). The main components in TSF were validated and quantified by thin-layer chromatography and high-performance liquid chromatography.

#### Concomitant treatments

Based on the 2013 American Diabetes Association (ADA) practice guidelines, all participants will receive standard treatments as follows:Irbesartan: Irbesartan will be selected as the basic treatment to lower proteinuria and protect renal function. All participants will take irbesartan orally at a dosage of 300 mg daily.Antihypertensive drugs: Participants with hypertension will receive antihypertensive drugs to maintain a blood pressure of ≤ 130/80 mmHg. Non-dihydropyridine calcium channel blockers or alternatively, beta blockers, will be the recommended drugs. If the blood pressure cannot be maintained at 130/80 mmHg by the combination of these two drugs, diuretics will be added.Blood glucose control therapy: The A1C of all participants will be controlled to ≤ 8.0 % throughout the trial. Metformin will be used for participants with eGFR above 60 ml/min. For participants with eGFR below 60 ml/min, oral repaglinide will be the alternative. For participants whose A1C cannot be controlled with oral agents, insulin will be used.Antilipemic agents: Participants with hyperlipidemia will receive atorvastatin.

Participants will also be instructed to follow a low-sodium diabetes diet, including a reasonable intake of calories, protein, carbohydrates, and fat. They will also be asked to exercise regularly. Administration of other medications will be at the discretion of the attending physician investigator and would not interfere with outcome assessments. Investigators will be instructed to record in the CRF the details of any additional/transformational drug or therapy, such as the name, dosage, and duration of administration.

#### Prohibited concomitant medications

During the trial period, use of any other drugs that could affect urinary protein or renal function will be prohibited. This includes TCMs that function to replenish *qi* and *yin* or promote blood circulation. Other prohibited agents include vitamin D, spironolactone, pentoxifylline, rhubarb sodium bicarbonate tablets, aminoglycoside antibiotics, nonsteroidal anti-inflammatory drugs, and antiviral drugs. If participants use any of the above-mentioned drugs, they will be withdrawn from the study.

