### Outcome measurements

#### Primary endpoint

The primary endpoint is 24 h UP. The change in 24 h UP from baseline to 24 weeks will be the analysis metric for the difference between the two groups. At baseline and treatment endpoint (24 weeks), the average values of two different samples collected within 1 week will be used to minimize variation between the different urine samples.

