### Statistical analysis

This trial will use three analysis sets: the intention-to-treat set, which will regard all participants as randomized regardless of whether or not they received the randomized treatment; the per protocol analysis set, which will be restricted to participants who complete the 24-week treatment and/or have the primary endpoint measurement records of at least three time points during the study; and the safety analysis set, which will include randomized participants who have made at least one visit. Multiple imputation analysis will be performed to account for the effect of missing data. Partially missing data will be carried forward with the principle of the last observation carried forward (LOCF). A *P* value less than 0.05 will be considered significant. SAS 9.2 software (SAS Institute, Cary, NC, USA) will be used for analysis.

Continuous variables will be expressed as the mean (SD), and categorical variables, as numbers and percentages. To compare baseline data between the two groups, independent *t* tests (or the Mann–Whitney U test) will be used to analyze continuous data, and chi-square or Fisher exact test will be used for categorical data. Outcome analysis will be performed using *t* test for normally distributed data and rank sum test for non-normal distribution data. Considering that the baseline 24 h UP and/or A1C are essential for the progression of urinary protein, analysis of covariance (ANCOVA) using 24 h UP and/or A1C as covariates will be performed to analyze the 24 h UP reduction at 24 weeks. To investigate the effects of treatment and time course, repeated measures analysis of variance (ANOVA) will be applied to determine changes in the 24 h UP and eGFR at each visit. For safety endpoints, incidences of DILI and BMS will be analyzed by Kruskal-Wallis test, and the incidence of QTc will be evaluated by a chi-square test. For AE evaluation, all AEs will be reported including its grade, time of occurrence, duration, treatment, prognosis, and correlation with the intervention drugs. The chi-square test or Fisher exact test will be used to compare the incidence of AEs between the two groups.

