### Participant retention and withdrawal

To prevent missing data and to avoid associated complexities in the study analysis, once a patient is randomized, investigators will make reasonable efforts to follow the patient for the entire study period. Efforts will include the following:Reimbursement of participants for public transportation costsScheduling and reminding participants of their return visitsReimbursing participants in the placebo group at the conclusion of the trial

Participants may withdraw from the study for any reason at any time, and the reason will be recorded in the CRF. Investigators can also withdraw participants from the study to protect their safety. Reasons that can prompt withdrawal include the following:Rapidly increasing serum creatinine of more than 50 % of baseline after 2 to 4 weeks of treatmentDecreasing eGFR of more than 50 % of the baseline after 2 to 4 weeks of treatmentDevelopment of severe complications and/or deterioration of an existing health condition

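### Prohibited-drug use ends study participation itself, so week-24 outcomes would go uncollected and be imputed, in conflict with the aim of full follow-up

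*Protocol article*

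**What the plan says.** Four parts of the protocol article bear on this point.

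- **Prohibited concomitant medications.** The general rule is that "use of any other drugs that could affect urinary protein or renal function will be prohibited". Named examples follow, among them vitamin D, spironolactone, nonsteroidal anti-inflammatory drugs and antivirals. The consequence is mandatory: "If participants use any of the above-mentioned drugs, they will be withdrawn from the study". No minimum dose or duration is given.
- **Participant retention and withdrawal.** To prevent missing data, "once a patient is randomized, investigators will make reasonable efforts to follow the patient for the entire study period". The same section then says "Investigators can also withdraw participants from the study to protect their safety". The reasons that can prompt this are a creatinine rise or an eGFR fall of more than 50 % of baseline after 2 to 4 weeks of treatment, and serious complications or worsening health.
- **Primary endpoint.** "The change in 24 h UP from baseline to 24 weeks will be the analysis metric for the difference between the two groups". Creatinine and eGFR change over the same interval are secondary endpoints.
- **Statistical analysis.** The main set is "the intention-to-treat set, which will regard all participants as randomized regardless of whether or not they received the randomized treatment". Missing data are to be handled by multiple imputation and by LOCF. The per-protocol set is "restricted to participants who complete the 24-week treatment and/or have the primary endpoint measurement records of at least three time points during the study".

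**The concern.** The prohibited-drug rule removes the person from the study, not only from study treatment. Nothing in the article separates the two or says that a withdrawn participant still gives a week-24 sample. The event comes after randomization, and the drugs are singled out because they may act on the outcome variables. The discretionary withdrawals are tied even more closely to renal course, since creatinine and eGFR are themselves endpoints.

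An intention-to-treat comparison needs week-24 values from these people. If the values are never measured, the set is complete only on paper and the result depends on how the gaps are filled. If withdrawal is related to outcome and its frequency differs between arms, the estimated effect can be biased, and a larger sample does not remove that.

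**Working it through.** **1. The sections side by side.**

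| Section | Effect on a randomized participant |
|---|---|
| Prohibited concomitant medications | Any use of a listed drug: withdrawal from the study, mandatory |
| Participant retention and withdrawal, reasons | Early renal worsening or deteriorating health: withdrawal from the study, at the investigator's discretion |
| Participant retention and withdrawal, aim | Reasonable efforts to follow to the end of the study |
| Statistical analysis, intention-to-treat | Counted as randomized, whatever treatment was received |

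The first row cannot be applied together with the third: the same participant cannot be both removed and followed. The second row is in tension with the third, but it is permissive and is listed as an exception in the same section. The fourth row keeps the person in the denominator without supplying a week-24 value.

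**2. What would replace the missing value.** Table 3 schedules 24 h UP at weeks 0, 4, 8, 16 and 24, then 28, 36 and 48. Under LOCF, withdrawal at 2 to 4 weeks carries forward the baseline value (a change of exactly zero) or the week-4 value. Later withdrawal carries forward week 8 or week 16. Multiple imputation in its usual form assumes that withdrawn participants resemble continuing ones with the same observed data. That is doubtful when withdrawal follows renal worsening.

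**3. Possible bias (illustration by assumption).** The article gives no rate of forced withdrawal, so there is no figure of the plan's own to reproduce. Let w be the proportion withdrawn in an arm and k the amount by which the withdrawn would have been worse at week 24. The completers' mean in that arm equals the full mean minus w × k. The shift in the completers' difference (TSF minus placebo) is therefore

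shift = (w_placebo − w_TSF) × k.

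Target difference −0.54, from the sample size section. It is described there as a difference of relative changes and is read here as grams, which is an assumption.

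| Withdrawal difference | k (g) | Shift (g) | Share of 0.54 |
|---|---|---|---|
| 5 points | 0.5 | 0.05 × 0.5 = 0.025 | 5 % |
| 10 points | 0.5 | 0.10 × 0.5 = 0.05 | 9 % |
| 10 points | 1.0 | 0.10 × 1.0 = 0.10 | 19 % |

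With 10 points more withdrawal on placebo, the difference becomes −0.49 to −0.44. With 10 points more on TSF, it becomes −0.59 to −0.64. With equal withdrawal and equal k, it stays at −0.54.

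**4. Scale against sampling error.** Pooled SD = √((0.91² + 0.95²)/2) = 0.93 g, from the preliminary-trial SDs. The planned 144 gives 72 per group; less 20 % dropout, 72 × 0.8 = 57.6, about 58. Standard error = 0.93 × √(2/58) = 0.17 g. The largest shift above is 0.10/0.17, about 0.6 of a standard error.

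**5. Power.** Assume that half of the 20 % dropout is protocol-forced: 0.5 × 0.2 × 144 = 14.4 outcomes. Keeping them gives 72 × 0.9 = 64.8, about 65 per group. Two-sided t-test power for 0.54 with SD 0.93 is 87.3 % at 58 and 90.7 % at 65. At the extreme, with all dropout forced and all of it kept, the normal approximation gives 87.6 % at 57.6 and 93.6 % at 72. Every value exceeds the planned 80 %.

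**6. The per-protocol set.** The and/or wording admits anyone with three primary-endpoint time points. If baseline counts, a participant who takes a prohibited drug after week 8 already has weeks 0, 4 and 8 and qualifies. If follow-up continued, almost all such participants would qualify.

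**The case against.** The strongest reply has four parts.

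- **Withdrawal for worsening is not automatic.** A reader might infer that everyone whose creatinine or condition worsens is removed. The retention section does not say so. Its wording is permissive, and the creatinine and eGFR reasons are limited to large changes after 2 to 4 weeks. A slow decline over 24 weeks does not meet them. This stands: only the prohibited-drug rule is mandatory.
- **No outcome is thrown away.** A reader might also infer that week-24 results are discarded or that the intention-to-treat set is defeated. The article keeps all randomized participants in that set and names methods for missing values. This stands too: the values go uncollected and are then imputed, which weakens the analysis but does not void it.
- **The figures have no anchor.** The withdrawal rates, the difference between arms and the outcome gap are all assumed. Products are identical and allocation is blinded, and the documents give no reason to expect different rates. Some prohibited-drug use will be unrelated to renal course. The formula describes completers, not the planned imputation. All of this stands, so the range is only illustrative.
- **The full protocol may say more.** It is not shown and could provide for data collection after withdrawal. That lowers confidence that outcomes are actually lost. It does not excuse an explicit rule in the article that says the opposite of the retention aim.

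It is also fair to say that an effect in the absence of prohibited drugs is a legitimate target. That is a reason to state how values after such use enter each analysis, not a reason to stop measuring.

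**Conclusion.** The point holds in limited form. The mandatory rule on prohibited drugs conflicts with the aim of following randomized patients throughout, and it leaves the intention-to-treat analysis to rely on LOCF or imputation for an outcome that could have been measured. The discretionary withdrawals add to this to an unknown extent.

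The documents fix neither the size nor the direction of any bias. Under the stated assumptions, and for completers only, it is about 0.03 to 0.10 g in either direction, or 5 to 19 % of the 0.54 target; it is zero if withdrawal and outcome gap are equal between arms. Power is a minor matter. The case for change rests on avoidable, possibly outcome-related missing data and on sections that cannot all be followed as written.

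**What to change.** Reconcile the sections on prohibited medications, on retention and withdrawal, and on statistical analysis:

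1. State that prohibited-drug use or a safety withdrawal is recorded with its date and reason and does not end outcome collection.
2. For participants not yet past week 24, continue the scheduled 24 h UP, creatinine and eGFR measurements unless consent is withdrawn.
3. Use the observed values in the intention-to-treat analysis, and keep imputation for values that are truly missing.
4. Handle prohibited-drug users through the per-protocol set, and amend its and/or criterion so that it excludes them. Without that amendment they would qualify on the number of measurements.

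The drug list, the thresholds and decisions on study treatment stay with the clinicians; the change concerns measurement and analysis only.

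The cost is a short amendment and a notice to the five sites; the visits and assays are already in Table 3. There are two downsides. The intention-to-treat estimate will include the effect of any prohibited drug taken. The gain is also partial: 123 of the planned 144 were already recruited when the article was written, and outcomes already missed cannot be recovered.
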